#### Interim analyses {21b}

Interim analyses will be conducted for DSMB reporting but will not be conducted for presentation or publication.

### Methods for additional analyses (e.g. subgroup analyses) {20b}

A sensitivity analysis including only participants who were adherent to the intervention will be conducted as outlined below.

### Methods in analysis to handle protocol non-adherence and any statistical methods to handle missing data {20c}

A sensitivity analysis including only participants who were adherent to their assigned study diet will be conducted. Participants in the MPE diet group will be included in the sensitivity analysis if DHQ-III survey indicate that they consumed within 20% of recommendations for key intervention diet components (≥ 5 cup equivalent servings of total fruit and vegetables). TROO ketogenic participants will be included in the sensitivity analysis if they achieved a ketogenic ratio (KR) value of > 1.5 on DHQ-III surveys or if they are determined to be in nutritional ketosis in 80% of the ketone readings throughout the trial. KR value ≥ 1.5 is considered the minimum threshold to predict a ketogenic diet and will be calculated as follows: (0.9*grams fat + 0.46*grams protein) divided by (0.1*grams fat + 0.58*grams protein + grams total carbohydrate – grams total fiber). Control participants will be excluded from the sensitivity analysis if they have a significant change in HEI 2020 scores, defined as 10 points or more in either direction from baseline values. In all analyses, missing data will be modeled within the GLMM framework, which provides better power and reduced bias compared to other methods to handle missing data.

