#### Ketone monitoring (TROO ketogenic group only)

Participants randomized to the TROO ketogenic diet will be provided a Keto-Mojo® blood ketone and glucose monitor for diet tracking purposes. Participants will be instructed to check blood ketones daily for 2 weeks or until they are firmly in ketosis. After 2 weeks, study participants will be allowed to reduce the frequency of checking ketones to 2 times per week. All testing supplies will be provided, including lancets and test strips, to provide immediate results on blood ketone values. The participants who are assigned to the TROO ketogenic diet will download the Keto-Mojo® application onto their smart phone and create a MyMojoHealth Account for themselves with the assistance of the study team. The study team will teach the participant how to test for ketones using the ketone meter and will show the participant how to synchronize the ketone readings from their ketone meter with their MyMojoHealth account. The participant will be asked to join the study team practice accounts so their assigned RDNs may access the data throughout the duration of the study.

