### Criteria for discontinuing or modifying allocated interventions {11b}

No modification of the interventions is anticipated throughout the trial. Reasons for discontinuation of study intervention include:*Cognitive impairment*: If the study participant demonstrates difficulty following or remembering study tasks, a member of the study team may repeat the SPMSQ. If a participant is identified as potentially having cognitive impairment, as assessed by the SPMSQ, and four or more errors are recorded, the study staff will notify the PI to discuss the participant’s cognitive state. The study staff will also send a letter to the participant’s neurologist to inform them that a potential decline in cognition has been observed with a recommendation to evaluate the participant’s cognition and competence as they deem appropriate. The neurologist will be informed if more than four errors were documented, which is a medical stop point. If the neurologist determines that the participant is cognitively impaired, the participant will not be allowed to continue in the study; however, if the treating neurologist reports that the patient is cognitively competent, the participant may continue the study intervention. If the participant’s SPMSQ score falls in the moderate range (5–7 errors) or if the participant’s neurologist deems them to have significant cognitive impairment, the participant will be instructed to discontinue the study intervention, although data collection will continue. If in the severe range (8–10 errors), the participant will stop all study activities and withdraw from the study because the data is considered unreliable.*Physical impairment*: If a study participant becomes physically impaired due to injury, an adverse event, loss of function due to MS or other diagnoses, they may still participate in the study intervention. Other study procedures such as motor and ocular assessments will be performed dependent on the task and impairment as appropriate. The changes in function will be captured in the extenuating circumstances electronic Case Report Form (eCRF) and adverse event forms in the database.*Pregnancy:* If a study participant becomes pregnant during the study, it will be documented in the REDCap data capture platform on the extenuating circumstances eCRF. The study participant will be instructed to follow the diet that is recommended by the medical team that is providing the participant’s pregnancy-related care. The participant may continue to complete other study procedures.*Treating physician no longer recommends*: If a study participant’s treating physician determines it is no longer in the participant’s best interest to continue with some or all of the study interventions, the participant may remain in the study and complete other study procedures. A participant’s treating physician may direct their patient to discontinue or withdraw from the study intervention if any clinical adverse event (AE), laboratory abnormality, or other medical condition or situation occurs such that continued participation in the study would not be in the best interest of the participant.*Participant discontinues on their own*: If a study participant discontinues part or all of the study intervention on their own, they may remain in the study and complete other study procedures. The study team will record when the study intervention was altered or discontinued via patient report.

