
### Strategies to improve adherence to interventions {11c}

Participants in the MPE diet group will be considered adherent to their diet if DHQ-III survey indicate that they consumed within 20% of recommendations for key intervention diet components (≥ 5 cup equivalent servings of total fruit and vegetables). Adherence to the TROO ketogenic diet will be determined by participants achieving a ketogenic ratio (KR) value of > 1.5 on DHQ-III surveys or by being in nutritional ketosis in 80% of the ketone readings throughout the trial. KR value ≥ 1.5 is considered the minimum threshold to predict a ketogenic diet and will be calculated as follows: (0.9*grams fat + 0.46*grams protein) divided by (0.1*grams fat + 0.58*grams protein + grams total carbohydrate – grams total fiber). In the event the study intervention becomes too restrictive or difficult for the study participant to maintain, the study team has created diet adherence guidelines to give participants options to ease the burden of the study intervention and prevent study discontinuation (Table 2). One of the senior investigators, who has extensive experience conducting long-term, randomized controlled dietary intervention trials, was unblinded and responsible for monitoring and supporting participant adherence to the dietary protocols.

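### The ketone route to TROO adherence has no minimum number or time span of readings and ignores the recorded stop date, so an early quitter can enter the adherent-only analysis

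*Protocol article*

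**What the plan says.** The section on non-adherence and missing data {20c} defines who enters the adherent-only sensitivity analysis. A TROO participant qualifies with a DHQ-III ketogenic ratio above 1.5 or, as the alternative, "if they are determined to be in nutritional ketosis in 80% of the ketone readings throughout the trial". The section on strategies to improve adherence {11c} gives the same alternative: "or by being in nutritional ketosis in 80% of the ketone readings throughout the trial". Neither section states a minimum number of readings, a period to be covered, or how a test not done is treated.

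The ketone monitoring section has participants "check blood ketones daily for 2 weeks or until they are firmly in ketosis". It continues: "After 2 weeks, study participants will be allowed to reduce the frequency of checking ketones to 2 times per week". Testing is done by the participant and synchronised from a meter, so each reading reaches the study dietitians.

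The section on discontinuing interventions {11b} says: "If a study participant discontinues part or all of the study intervention on their own, they may remain in the study". It adds that the team records, from the participant's report, when the intervention was changed or stopped. Neither adherence section refers to that record.

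**The concern.** A percentage of readings measures adherence over a period only if the readings span that period. Here the participant decides when to test, and someone who abandons a ketogenic diet has little reason to go on testing. If the readings end when the diet ends, the off-diet months add nothing to the denominator and the score stays at its early level. The two criteria are joined by *or*, so the meter score alone is enough, whatever the DHQ-III shows at months 12 and 24.

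This is the only planned analysis whose population is defined by following the diet. The per-protocol analysis in section {20a} selects on having the 6-month or 24-month assessments, so an early quitter who stays in follow-up remains in that one too. If such people count as adherent, the TROO arm of the sensitivity analysis mixes on-diet and off-diet outcomes, and the reported TROO adherence is too high.

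**Working it through.** The 80% is a chosen cut-off, so there is no derived figure to reproduce. The check applies the rule to someone who stops both diet and testing early.

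**Inputs**
- Diet duration: 24 months (Intervention description {11a}), taken as 104 weeks.
- Testing: daily for 2 weeks, then twice weekly (Ketone monitoring). The section allows variation, so exactly 14 daily readings and exactly 2 a week afterwards are assumptions.
- Threshold: 80% ({11c} and {20c}).
- DHQ-III: months 0, 3, 12 and 24 (Dietary assessment).

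**Expected readings over the trial:** 14 + 2 × (104 − 2) = 218.

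**Readings by a stop at week w:** n = 14 + 2 × (w − 2). The smallest passing count is 0.80 × n, rounded up.

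| Stop at week | Readings taken | Needed to pass | Share of readings taken | Share of 218 |
|---|---|---|---|---|
| 2 | 14 | 12 | 85.7% | 5.5% |
| 6 | 22 | 18 | 81.8% | 8.3% |
| 13 | 36 | 29 | 80.6% | 13.3% |
| 26 | 62 | 50 | 80.6% | 22.9% |
| 52 | 114 | 92 | 80.7% | 42.2% |

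**Worked case:** a week-6 quitter with 20 of 22 in ketosis scores 20/22 = 90.9% and passes. Against the expected total this is 20/218 = 9.2%.

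**Sensitivity to the assumed schedule**, again for a stop at week 6 with the smallest passing count:
- Daily testing for 1 week only: expected 7 + 2 × 103 = 213; taken 7 + 2 × 5 = 17; 14 of 17 passes (82.4%), which is 14/213 = 6.6% of expected.
- Daily testing for 4 weeks: expected 28 + 2 × 100 = 228; taken 28 + 2 × 2 = 32; 26 of 32 passes (81.3%), which is 26/228 = 11.4% of expected.

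The count moves, but the classification does not.

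**The same person when coverage is required.** If ketosis is assessed by week and weeks without a reading do not count, the week-6 quitter reaches at most 6/26 = 23% of weeks to month 6 and 6/104 = 6% of weeks to month 24. Both are far below 80%.

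**The case against.** Four objections deserve an answer.

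- **The denominator is not stated.** A reader might infer that the rule is fixed as readings actually taken. The text does not say so: its reference to the whole trial could mean readings scheduled, or coverage of the full period. This stands. Readings that exist are the natural meaning but not the only one. The two meanings classify the same early quitter in opposite ways, so the ambiguity itself needs settling.
- **Such detail may sit in an analysis plan that is not shown.** This carries some weight for the handling of missed tests. However, the article gives an operative rule twice, with thresholds and a formula, and that rule as written admits the early quitter.
- **Early quitters may fail anyway.** Days spent entering ketosis count against them. With five non-ketotic readings, a week-6 quitter has 17/22 = 77% and fails. This is correct; with four, 18/22 = 82% and the person passes. So some early quitters pass, not all.
- **Only a sensitivity analysis is touched.** This is correct, and it limits the importance of the point.

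A reader might also infer the mirror-image fault, that someone on the diet for all 24 months with ketosis in 75% of readings is wrongly shut out. The documents do not support that. Such a person still qualifies with a ketogenic ratio above 1.5, and 163/218 = 74.8% misses the meter criterion whether readings taken or readings expected form the denominator. That is a consequence of choosing 80%, not of missing coverage.

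**Conclusion.** The point holds in a limited form. Sections {11c} and {20c} set no minimum number or time coverage for ketone readings and leave the recorded stop date unused. Under the natural reading, a participant who leaves diet and meter early with mostly ketotic readings is analysed as adherent, on as little as 5.5% (stop at week 2) to 13.3% (stop at week 13) of the roughly 218 expected readings. A low ketogenic ratio on later surveys does not prevent this.

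The conclusion assumes that some quitters stop testing but remain in follow-up. That is plausible and permitted by section {11b}, but the documents give no number. It would therefore go too far to say that the TROO estimate is biased by a known amount or in a known direction. Dilution towards no effect is likely if the diet works, but it cannot be quantified here. The intention-to-treat primary analysis is not affected.

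**What to change.** Amend {11c} and {20c} in the same words, before adherence is classified:

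1. Tie the ketone criterion to the outcome time point: month 6 for patient-reported outcomes and month 24 for clinical assessments. Require readings to cover that period. One way is to assess ketosis by week or by month, with an interval that has no reading not counted as in ketosis on this route. This also stops the daily readings of the first two weeks from outweighing later weeks, and it avoids relying on an exact count of readings due, which the flexible schedule does not define.
2. Class a participant with a recorded permanent discontinuation of the diet itself before that time point as non-adherent by either route. Stopping only the supplements, or a brief modification of the kind the retention section {18b} permits, should not trigger this.

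The cost is mainly analysis wording, since meter readings are synchronised and stop dates are recorded. The team should check that those records separate the diet from supplements and a permanent stop from a temporary one. The drawback is that some participants who stay on the diet but rarely test will fail the ketone route. They may still qualify through the ketogenic ratio, but no DHQ-III is scheduled at month 6, so the plan should say which survey serves for that time point.

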### Sample size {14}

Sample sizes required to achieve 80% power for testing between-treatment changes over time were calculated for each measure using summary statistics at baseline and 6-months from our previous randomized parallel arm trial comparing the LSF and MPE diets.

Using a group sample size of 36 and an alpha of 0.05, power and estimates for mean difference within and between groups are shown in Table 4. To ensure adequate sample size at the primary endpoint of the study, we will enroll enough participants to cover a 33% attrition rate in each group, giving a final target enrollment sample size of *n* = 54 per group.

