### Dietary assessment

Dietary assessment will be collected by asking study participants to complete the DHQ-III survey at months 0, 3, 12, and 24. Additionally, participants randomized to the MPE or TROO ketogenic diets will be instructed to record key study diet components each day using a study specific three-item questionnaire in the study-related (MyCap) application on their smart device. To decrease participant burden, completing MyCap is optional. The Healthy Eating Index (HEI), which is designed to determine how closely dietary intake mirrors the DGA, will be applied to the usual care control group to determine adherence to the DGA.

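### The adherent-only sensitivity analysis admits MPE participants on evidence of adherence but keeps controls by default, so those without a follow-up diet survey leave MPE and stay in control

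*Protocol article*

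**What the plan says.** Section {20c} of the protocol article states the aim: "A sensitivity analysis including only participants who were adherent to their assigned study diet will be conducted". It then gives one rule per arm.

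- **MPE:** "Participants in the MPE diet group will be included in the sensitivity analysis if DHQ-III survey indicate that they consumed within 20% of recommendations". These recommendations concern the key components of that diet. No other route is given.
- **TROO ketogenic:** "TROO ketogenic participants will be included in the sensitivity analysis if they achieved a ketogenic ratio (KR) value of > 1.5 on DHQ-III surveys". A second route needs no survey: ketosis shown by 80% of a participant's own ketone readings.
- **Control:** "Control participants will be excluded from the sensitivity analysis if they have a significant change in HEI 2020 scores". The threshold is a shift of at least 10 points, up or down, relative to baseline.

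Under Dietary assessment, participants are to "complete the DHQ-III survey at months 0, 3, 12, and 24", and the same paragraph applies the HEI to controls. Section {18a} schedules the patient-reported outcomes at baseline and every 6 months. Section {20c} ends by saying that missing data will be modelled within the GLMM.

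**The concern.** The rules have opposite defaults. An MPE participant is out until a survey puts them in; a control is in until a survey puts them out. With no usable post-baseline DHQ-III, the MPE participant cannot meet the inclusion condition. A control in the same position has no computable HEI change and cannot meet the exclusion condition. The same missing form therefore has opposite consequences in the two arms.

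The GLMM sentence does not resolve this. It concerns missing values among people already in the model, and does not say who belongs to the analysis set.

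A reader will take this analysis as the effect among people who kept to their allocation. As worded, part of the control arm may be people whose diet was never verified, while MPE contains none. If people who skip the survey also fare worse, the contrast favours the diet for a reason unrelated to diet. This is separate from whether the adherence cut-offs are well chosen.

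**Working it through.** **1. The plan's own figure.** Section {14} starts from 36 per group and says "we will enroll enough participants to cover a 33% attrition rate in each group". 36 / (1 − 0.33) = 53.7, rounded up to 54; 3 × 54 = 162. Both stated figures reproduce. The allowance is 54 × 0.33 = 17.8, about 18 per arm.

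**2. The rules side by side, for a participant with no usable post-baseline DHQ-III.**

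| Arm | Default | Result without the survey |
|---|---|---|
| MPE | out | out |
| TROO | out | out, unless ketone readings qualify |
| Control | in | in |

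Two steps are inferred. The MPE rule does not say which survey counts, but a month 0 survey cannot show adherence to a diet not yet begun. That the HEI is derived from the DHQ-III follows from its place under Dietary assessment.

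**3. Size of the tilt.** Assume no diet effect, and a change in MSQoL-54 that is *d* points worse in participants without the survey, equally in every arm. Let *f* be their share of the controls who are retained and supply the outcome. Then

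bias in the MPE-control difference = *f* × *d*, in favour of MPE.

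Take *d* = 5, the change that the article calls clinically significant. Using it as the deficit is an assumption, and so are the shares below. No surveyed control is excluded for HEI change in this table.

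| Scenario | *f* | Bias (points) |
|---|---|---|
| 5% of the arm lacks the survey, all give QoL | 0.05 | 0.25 |
| 18 of 54 lack it, a quarter give QoL | 4.5/40.5 = 0.11 | 0.56 |
| 18 of 54 lack it, half give QoL | 9/45 = 0.20 | 1.0 |
| 18 of 54 lack it, all give QoL (extreme) | 18/54 = 0.33 | 1.67 |

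With 15% affected and *d* = 3, the bias is 0.15 × 3 = 0.45 points. Removing surveyed controls for HEI change raises *f*. If 10% to 30% of them go, the 5% scenario moves to 0.28–0.35 points and the extreme to 1.8–2.1.

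**4. Against sampling error.** With an assumed SD of change of 12, the extreme case has 36 in MPE and 54 in control. The control variance is 144 + 25 × (1/3) × (2/3) = 149.6, so SE = √(144/36 + 149.6/54) = 2.60. The bias is 1.67/2.60 = 0.64 SE, and a simple two-group test at a nominal 5% rejects about 10% of the time. If the Bonferroni correction in {20a} also governs this analysis with three comparisons, the rate is about 4.1% against 1.7%. In the 5% scenario the nominal rate is 5.1%.

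**5. Effect of aligning the rule.** Let *m* be the share without the survey and *c* the share of surveyed controls with an HEI change of 10 or more. Controls kept as written = 54*m* + 54(1 − *m*)(1 − *c*); under an aligned rule, 54(1 − *m*)(1 − *c*). With *c* = 0.1 (assumed):

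- *m* = 5%: 48.9 becomes 46.2.
- *m* = 10%: 49.1 becomes 43.7.
- *m* = 33%: 50.4 becomes 32.6.

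The MPE set does not change.

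**The case against.** The strongest reply is that {20c} never says how a participant without a survey is classed, and that an analysis plan not shown could settle it. The opening sentence, limiting the set to adherent participants, could also be read as excluding controls of unknown diet. That stands in part: the consequence is deduced from the rules, not declared. But the article does more than leave a gap. It fixes a rule for each arm, the rules point in opposite directions, and a plan that followed them would inherit the asymmetry.

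The affected group is also likely to be small. A DHQ-III is due at month 3, alongside an in-person visit whose payment follows completion of assessments and surveys, so someone lost after month 6 would usually already have one. The month 12 and 24 surveys coincide with quality-of-life collection. This stands, and it is why the lower scenarios are the realistic ones.

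Three stronger readings are tempting and not supported:

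- **That a third of each arm is affected and the false-positive rate doubles to 10%.** The 33% covers attrition at the primary endpoint, so mostly people without the 6-month outcome. A control with only baseline data adds little to estimated change in the GLMM. The 10% also ignores the Bonferroni correction and comes from a two-group comparison, not the planned model.
- **That both diet arms need a survey to enter.** TROO has the ketone route, so the clean contrast is MPE against control.
- **That the main result is compromised.** Section {20a} makes the primary analysis intention-to-treat in all randomized participants.

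**Conclusion.** The asymmetry is in the text and should be removed, but it is minor. It concerns one sensitivity analysis, and chiefly participants who supply post-baseline MSQoL-54 without a usable post-baseline DHQ-III. If they do worse than those who return the survey, the MPE-control contrast favours the diet, probably by a few tenths of a point to about 1 point; about 1.7 points is an extreme case, not an expectation. The direction rests on that assumption, and the size on an assumed deficit of up to 5 points and on assumed shares that the article does not give. If the participants without the survey do no worse, the mean does not shift, but the control set still contains unverified people in an analysis described as adherent-only.

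**What to change.** In {20c}, word the control rule in the same direction as the diet arms: a control is included only if a post-baseline DHQ-III at the named time point shows an HEI 2020 change of less than 10 points from baseline. Also:

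- Name the DHQ-III time points that count for each endpoint. None is scheduled at month 6, so the month 6 analysis has to point to another survey, for example month 3.
- Keep TROO's ketone-reading route as stated. Requiring a DHQ-III in every arm would override it.
- Report by arm the number excluded for missing adherence data, separately from the number excluded for non-adherence.

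This takes a few sentences and uses data already being collected. The cost is a smaller control set in this analysis, by the number of controls without the survey: about 3 of 54 if 5% lack it, and about 18 in the extreme case, which would not be a small loss.

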## Interventions

### Explanation for the choice of comparators {6b}

Since nutrition counseling is not a current clinical recommendation for individuals with MS, the usual care control group will not receive diet education from the study RDN. Instead, they will receive educational materials and resources from the 2020–2025 DGA and be allowed to utilize the resources to any degree of compliance. The rationale for providing only educational materials on the DGA to the usual care control group is that: 1) nutrition counseling and education provided by RDNs is not part of the standard of care for MS in the U.S. and 2) that people with MS are recommended to follow a general healthy diet such as the DGA. Giving study participants educational material on the DGAs and the choice to follow the DGA recommendations to any degree of compliance maintains clinical equipoise of the usual care control.

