#### Elimination and re-introduction phase (MPE group only)

At baseline (month 0), study participants assigned the MPE diet will be instructed to eliminate gluten, dairy, and eggs from their diet. In addition, at visit 2 (month 3), participants will also be instructed to eliminate all grains (including gluten-free), all legumes including peanuts and soy, and nightshade vegetables including tomatoes, potatoes, eggplants, and peppers for 3 months. After 3 months, study participants will be allowed to re-introduce one ingredient at a time, one ingredient per week. Study participants will be asked to keep a symptom diary and record any worsening mental or physical symptoms. If there are foods identified that cause a worsening of symptoms the study participant may remove the food item again. Participants may choose to re-introduce the food again if they desire to confirm whether the food is associated with worsening mental or physical symptoms. If symptoms again recur, the food may be eliminated from their diet for the remaining duration of the study.

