### Statistical methods

#### Statistical methods for primary and secondary outcomes {20a}

Data for this study will be stored electronically using the REDCap platform at the University of Iowa and analyzed in SAS® 9.4. Baseline demographic and clinical measures collected will be summarized and tested for differences between study groups. Categorical measures are displayed as counts (percentages) and use Pearson’s chi-square or Fisher’s exact tests, depending on expected crosstab counts. Continuous measure distributions will be assessed using histograms. Normally distributed measures will be displayed as means (standard deviations) and compared using two-sample t-tests. Non-normally distributed measures will be displayed as medians (interquartile ranges) and compared using the Wilcoxon rank sum test.

The generalized linear mixed modeling (GLMM) [76] framework will be used to test the main and interacting effects of diet and time on the outcome measures of interest while accounting for repeated measures from each participant. The GLMM framework allows for non-normal distributions among the outcome measures. Other potentially important variables (age, sex, BMI, baseline smoking status, baseline alcohol use, walking assistance, years of MS, DMT use, baseline vitamin D, baseline 6-min walk distance) will be considered for inclusion in each model to assess their relationship with the outcome and to determine if they modify the estimates for the diet and time interaction. For each unique model (outcome and predictor set combination), Akaike information criterion (AIC) [77] will be obtained and utilized for model selection. Point estimates, 95% confidence intervals, and p-values of the diet mean changes in outcome measures over visits will be generated for each optimal model. For primary data analysis, data from all participants randomized at baseline will be included in an intention-to-treat analysis. A secondary per-protocol analysis will be used to examine the participants who complete the primary endpoint at 6 months for patient-reported outcomes or had clinical outcome assessments at 24 months. Hypothesis testing of the main effects in each optimal model (according to AIC) will use the Bonferroni correction for multiple comparisons between the three study treatment arms. All analyses will be conducted with two-sided tests (alpha = 0.05) using SAS software version 9.4 (SAS Institute Inc.).

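### The adherent-only analysis excludes controls for a diet change their allocation permits, and its diet-arm rules omit the MPE eliminations and use ketone readings from after month 6

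*Protocol article*

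**What the plan says.** The primary analysis is intention-to-treat (Protocol article, Statistical methods {20a}). Section {20c} adds a sensitivity analysis restricted to participants who kept to their assigned diet.

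**Controls.** "Control participants will be excluded from the sensitivity analysis if they have a significant change in HEI 2020 scores", such a change being "defined as 10 points or more in either direction from baseline values". Three other places bear on what adherence means for this arm:
- Explanation for the choice of comparators {6b} lets controls use the DGA resources as much or as little as they wish, and argues that "the choice to follow the DGA recommendations to any degree of compliance maintains clinical equipoise of the usual care control".
- Dietary assessment says the HEI "will be applied to the usual care control group to determine adherence to the DGA".
- The usual care paragraph under Dietary education and resources says controls keep their existing eating habits while receiving DGA material.

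**MPE arm.** The one component printed in the rule is fruit and vegetables, at 5 or more cup equivalents with a 20% tolerance. The section on the elimination phase says that from month 0 participants "will be instructed to eliminate gluten, dairy, and eggs from their diet". A second set (grains, legumes, nightshades) is removed from month 3 for three months, and stepwise re-introduction is then allowed.

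**TROO arm.** A participant qualifies through a ketogenic ratio above 1.5 on DHQ-III, or by being "in nutritional ketosis in 80% of the ketone readings throughout the trial".

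**Timing.** Participants "complete the DHQ-III survey at months 0, 3, 12, and 24". Section {20a} places the patient-reported primary endpoint at 6 months.

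**The concern.** If controls may take up the DGA freely and HEI measures that uptake, a control whose HEI rises by 10 points is within allocation and, on the protocol's own measure, more adherent. An analysis meant to keep the adherent removes that person. Should controls improve on average, the rule strips out mainly those whose diet got better, and the remaining controls are set against diet-arm participants selected for success.

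On the diet side, an MPE participant who ate gluten, dairy and eggs throughout could count as adherent. A TROO participant's inclusion in a 6-month comparison could be decided by what happened between months 6 and 24, which the 6-month result may itself have influenced. At stake is whether the planned adherence result can be interpreted. The primary test is not at stake.

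**Working it through.** **1. The plan's own figure.** 36 evaluable per group with 33% attrition: 36 / (1 − 0.33) = 53.7, rounded up to 54, and 3 × 54 = 162. This reproduces the stated enrolment. Nothing below disputes it; 36 serves only as a base.

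**2. Share of controls dropped.** Inputs: the 10-point limit ({20c}); a normal HEI change with mean m and SD s, both assumed because the documents give neither; one follow-up survey compared with baseline.

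P(dropped) = [1 − Φ((10 − m)/s)] + Φ((−10 − m)/s)

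| m | s | up | down | dropped | left of 36 |
|---|---|---|---|---|---|
| 0 | 8 | 0.106 | 0.106 | 21% | 28.4 |
| 0 | 10 | 0.159 | 0.159 | 32% | 24.6 |
| 0 | 12 | 0.202 | 0.202 | 40% | 21.4 |
| 5 | 8 | 0.266 | 0.030 | 30% | 25.3 |
| 5 | 10 | 0.309 | 0.067 | 38% | 22.5 |
| 5 | 12 | 0.338 | 0.106 | 44% | 20.0 |

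**3. Precision when change is symmetric.** With a diet arm held at 36, the standard error of the difference grows by √[(1/36 + 1/n)/(2/36)]. For n = 28.4 this is √1.134 = 1.06; for n = 21.4 it is √1.341 = 1.16. The loss is 6% to 16%.

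**4. Shift in the control mean.** Let r be the correlation between HEI change and QoL change (assumed 0.2 to 0.4), a = (−10 − m)/s and b = (10 − m)/s. The mean QoL change among retained controls shifts by r × [φ(a) − φ(b)] / [Φ(b) − Φ(a)] SDs.
- m = 0: the numerator is zero, so there is no shift.
- m = 5, s = 10: (0.130 − 0.352)/0.625 = −0.356, giving −0.07 at r = 0.2 and −0.14 at r = 0.4.
- Over s = 8 to 10, simulation gives −0.04 to −0.09 SD at m = 3 and −0.07 to −0.15 SD at m = 5.

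A lower control mean favours the diet arms.

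**5. Selection in a diet arm.** Keeping the most adherent share p of an arm, with the same r and no diet effect, raises its mean by r × φ(c)/p, where c is the cut point. At p = 0.8 and r = 0.2: 0.2 × 0.280/0.8 = 0.07 SD. At p = 0.5 and r = 0.4: 0.4 × 0.399/0.5 = 0.32 SD.

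**6. Ketone window.** Ketone monitoring asks for daily readings for about 2 weeks and then allows two a week. Taking 26 and 104 weeks for months 6 and 24, and the minimum frequency:
- To month 6: 14 + 24 × 2 = 62 readings.
- To month 24: 14 + 102 × 2 = 218 readings.
- After month 6: 156/218 = 72% of the readings that decide inclusion.

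A participant in ketosis at all 62 readings and none afterwards scores 62/218 = 28% and fails this route. One in ketosis at all 156 later readings needs only 19 of the first 62 (31%) to reach 175 of 218, which is 80%.

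**7. MPE rule against the survey dates.** The eliminations in force from month 0 can be looked for in the month-3 DHQ-III. The second set starts at month 3 and runs three months. The month-3 survey falls at its start and the month-12 survey after re-introduction is allowed, so no scheduled survey follows that phase closely.

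**The case against.** The control exclusion has a rationale. If controls are meant to keep their existing diet, as Dietary education and resources says, a stable HEI is a sensible marker of a control who did so. The rule also works in both directions, so it removes controls whose diet worsens. Both points stand. A reader might infer that the plan discards controls for improving and so certainly favours the diets; the text does not support that. Step 4 shows no shift in the control mean when change is symmetric. A net gain is an assumption, though a plausible one: dietitians review the DGA with controls and help install the MyPlate application, and DGA material arrives monthly.

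Whole-trial ketone adherence suits a 24-month outcome, and {20c} does not limit the analysis to month 6. That also stands, so the objection applies only to month-6 contrasts.

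Tables 1 and 2 are not shown and may list further diet components. Even so, {11c} and {20c} both print only fruit and vegetables.

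Two tempting additions carry little weight. The ketogenic ratio appears both as above 1.5 and as at least 1.5, but it is a continuous quantity, so almost nobody would be reclassified. The set described by "A secondary per-protocol analysis will be used to examine the participants who complete the primary endpoint at 6 months" is a completer set, but {20a} says who is in it, so its name is a matter of labelling.

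Nor do the documents say that the adherent-only result will be offered as confirmation of the intention-to-treat result.

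**Conclusion.** The point holds as a conflict between sections and a poorly fitted set of inclusion rules in a non-primary analysis. Sections {6b}, Dietary assessment, Dietary education and resources, and {20c} cannot all be right about what adherence means for a control.

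The size is illustrative because every HEI input is assumed. With no mean change the rule costs 21% to 40% of controls and some precision. With a mean gain of 3 to 5 points and a correlation of 0.2 to 0.4, it lowers the control mean by about 0.04 to 0.15 SD in the diets' favour. Diet-arm selection of the kind in step 5 would act in the same direction, although a criterion as loose as the printed MPE one may select only weakly.

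That the MPE rule omits the eliminations, and that the ketone route reaches past month 6, follows from the text without assumption. The ratio and ketone measures do capture the ketogenic part of the TROO diet.

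**What to change.** - State once what adherence means for controls and bring the four sections into line. Keep all randomised controls in this analysis and report their HEI change descriptively.
- For month-6 outcomes, define adherence from the month-3 DHQ-III and ketone readings up to month 6. Use whole-trial data only for month-24 outcomes.
- Add to the MPE criterion the eliminations that DHQ-III can measure at each survey. At month 3 these are the ones in force since month 0; grains, legumes and nightshades cannot be scored then because their removal only begins at that visit.
- Label the result a non-randomised comparison.

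A complier-average estimate with randomised arm as instrument is optional. It requires allocation to act only through adherence, which is doubtful when only the diet arms receive study supplements and continuing dietitian support.

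The cost is revised analysis wording, some extra programming on data already being collected, and a less selective control set. Study activities are expected to run to September 2026, so the rules can be settled before the final analysis.
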